### Study Proceedings Including Data Collection

Participants will be screened by a resident dentist or a research assistant via the appointment scheduling system for any dental procedure. Since DFA can arise from multiple procedures, such as simple cleaning to teeth extraction. A research assistant will review consent with participants and parents. Written consent by the parents or legal guardian—including the child’s assent (if possible)—will be obtained on arrival at the clinic, the day of the procedure, while completing the preprocedural questionnaire. After verifying that the participant meets all inclusion and exclusion criteria, the research assistant will log into REDCap only 10 minutes before the start of the intervention to minimize the risk of bias toward the intervention, obtain the group allocation, and then announce it to the participant. Because of the nature of VR, no blinding will be possible to staff, participants, parents, or legal guardians. Baseline data collection prior to the dental procedure, including a sociodemographic questionnaire, recording of physiological parameters, and SAA sampling, will take approximately 15 minutes to complete. The VR headset will be adjusted to the child’s size, and approximately 5 minutes will be allotted for the child to familiarize themselves with the room, equipment, and the game (VR or cartoon on TV or tablet) before the start of the procedure. The intervention will last the entire dental procedure, and its duration will be documented for each patient. DFA assessment by proxy using the VARS will be performed on site by the research assistant present. As per the clinic’s protocol, if a child becomes restless and uncooperative, they will be held by parents for the remainder of the procedure if it cannot be safely stopped at this time or if the procedure is considered an emergency. If the procedure can be safely stopped, rescheduling will be discussed with the parents, including the possible need for sedation. The involvement of parents will be recorded, as will any other distractions used during treatment, such as stickers, teddy bears, music, and others. The occurence of side effects and medications used will be recorded. The former will be transmitted to the ethics committee if they are serious or life-threatening. As VR has the potential to cause nausea, dizziness, and motion sickness, if participants experience any of these, they will be managed in accordance with the clinic’s protocols.

If participants experience severe side effects, the treatment will be safely discontinued. All instruments in the mouth will be removed. The VR device will be removed from the participant. The dental chair will be adjusted to a comfortable position, and the patient will rest until they feel comfortable and recovered. The option to continue the treatment (without the VR headset) or to postpone it to another day will be discussed. Postprocedure SAA sampling and completion of questionnaires on parents’ and health care professionals’ satisfaction levels will take approximately 10 minutes. Equipment used by children will be disinfected and reset before the next participant.

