#### Study Time Periods

The study time periods are as follows and are detailed in Table 3. T0 corresponds to the time before the start of the intervention, T1 represents the time during or at the midpoint during the procedure, and T2 corresponds to the period 10 minutes after the intervention.

**Table 3. T3:** Study time periods and outcomes.

Study time periods	Outcomes									
	Patients’ SDC^a^	VARS^b^ anxiety	SAA^c^	Parents’ and health care professionals’ satisfaction	Patients’ satisfaction	Patients’ physiological parameters	VBRS^d^ behavior	Side effects	Length of procedure	FLACC-R^e^
T0^f^	✓	✓	✓			✓	✓	✓		✓
T1^g^		✓				✓	✓			✓
T2^h^			✓	✓	✓	✓		✓	✓	

a SDC: sociodemographic characteristics.

b VARS: Venham Anxiety Rating Scale.

c SAA: salivary alpha-amylase.

d VBRS: Venham Behavioral Rating Scale.

e FLACC-R: Face, Legs, Activity, Cry, and Consolability—Revised.

f T0: before the procedure.

g T1: midpoint during the procedure.

h T2: 10 minutes after the procedure.

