#### Measures of Primary Outcomes

The first primary outcome will evaluate DFA using the VARS (Table 1) [25]. The VARS is an observation-based assessment by proxy for DFA and is among the most frequent anxiety scoring instruments for DFA [25]. The scale has been used as an anxiety rating scale in other studies that evaluated the efficacy of VR distraction in the management of DFA [32,33]. The anxiety scale consists of one item, with six defined anxiety levels that range from 0, representing the child being relaxed, smiling, and willing to cooperate, to 5, representing the child being out of contact with the reality of the threat. The highest score represents the highest anxiety level [25]. A high degree of reliability was observed for this scale, even by untrained observers [25,34]. A research assistant will indicate a score from 0 to 5 on the anxiety scale at T0 and T1 (Table 3).

The second primary outcome will assess the mean difference in SAA levels between T0 and T2, 10 minutes after the dental procedure. This enzyme is linked to both adrenaline and noradrenaline and is a validated and reliable specific biomarker of autonomic nervous system activity. It has been proposed as an alternative biomarker for anxiety, over salivary cortisol, as it reaches peak levels within 10 minutes after a stressful procedure compared to cortisol, which requires a 30-minute delay [16,35]. Enzyme sampling has been performed in previous studies to evaluate DFA in children undergoing dental procedures [35-37]. This enzyme is considered an accurate and noninvasive procedure for assessing anxiety-related events such as dental examination, cleaning, restoration, or extraction in children [26,35]. Alpha-amylase sampling has been performed in previous studies to evaluate DFA for children undergoing dental procedures [35,38]. Salivary samples will be collected using a sterile dental cotton swab from under the tongue and stored immediately within a sterile vial in a research-specific on-site freezer at −80 degrees Celsius. The research assistant will collect the samples and take them to the laboratory. Results will be entered in REDCap for analysis purposes after the study.

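### The visit sequence and the definition of T0 let the salivary alpha-amylase baseline, and by inference the VARS baseline, be measured after the arm has been announced

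*Protocol article*

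**What the plan says.** The section Study Proceedings Including Data Collection is the only step-by-step account of the visit. After consent and the eligibility check, "the research assistant will log into REDCap only 10 minutes before the start of the intervention". The stated purpose of this late login is to limit bias. The assistant is then to "obtain the group allocation, and then announce it to the participant". The next sentence states that "no blinding will be possible to staff, participants, parents, or legal guardians". Baseline collection comes next in the text: the questionnaire, "recording of physiological parameters, and SAA sampling, will take approximately 15 minutes to complete". Headset fitting follows, and "approximately 5 minutes will be allotted for the child to familiarize themselves with the room, equipment, and the game".

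Under Study Time Periods, "T0 corresponds to the time before the start of the intervention". Neither randomization nor disclosure of the arm is mentioned there. Table 3 places VARS, SAA, physiological parameters, VBRS and FLACC-R at T0.

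Under Measures of Primary Outcomes, a research assistant scores VARS at T0 and T1. For SAA, "The second primary outcome will assess the mean difference in SAA levels between T0 and T2". Under Statistical Analysis, VARS at T1 is analysed by ANCOVA with the T0 anxiety or behavioral score as a covariate. SAA at T2 is analysed by ANCOVA with T0 SAA as a covariate.

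**The concern.** Adjusting for a baseline is safe in a randomized trial because allocation cannot have influenced it. A T0 value taken after the child has heard which arm it is in loses that protection. A child may be pleased, disappointed or newly apprehensive. The article itself describes SAA as a marker of autonomic activity that peaks within 10 minutes of a stressful procedure, so a reaction to the announcement could plausibly show in saliva taken minutes later. A T0 VARS rating made at that stage would also come from an unblinded observer. ANCOVA would then remove part of an effect of allocation, or add to it, and the result would be reported as the adjusted treatment difference.

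**Working it through.** **1. Timeline.** Inputs, all from Study Proceedings: login 10 minutes before the intervention, baseline about 15 minutes, familiarization about 5 minutes. Whether familiarization belongs to the intervention is not stated, so both readings are shown. Times are minutes relative to the start of the dental procedure.

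| | Intervention starts with the procedure | Intervention starts with familiarization |
|---|---|---|
| Arm announced | -10 | -5 - 10 = -15 |
| Needed after the announcement, in the narrated order | 15 + 5 = 20 | 20 |
| Available | 10 | 15 |
| Shortfall | 10 | 5 |
| Baseline run back to back, -20 to -5: minutes after the announcement | 5 | 10 |
| Latest baseline start if all of T0 is to precede the announcement | -10 - 15 = -25 | -15 - 15 = -30 |

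The narrated order cannot be followed with the stated durations. If baseline and familiarization run straight up to the procedure, the last 5 or 10 minutes of baseline still fall after disclosure. Only an earlier schedule, which the article does not state, puts all of T0 before it.

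**2. The planned SAA difference, for scale.** Sample and Setting gives log SAA changes of 0.171 (SD 1.05) in controls and -0.096 (SD 0.495) with VR. The difference is 0.171 - (-0.096) = 0.267. The normal approximation at two-sided α = 0.025 and 80% power gives n per group = (1.05² + 0.495²) × (2.241 + 0.842)² / 0.267² ≈ 180. The Welch t calculation gives 182 (power 80.1%), which reproduces the stated 364. So 0.267 is taken as the planned difference.

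**3. Bias.** ANCOVA estimates (arm difference at T2) - slope × (arm difference at T0). If disclosure shifts T0 by δ between arms, the estimate moves by slope × δ in absolute size. Neither quantity is in the article. The assumed ranges are δ from 0.05 to 0.20 log units and slope from 0.3 to 1.0. Power and rejection rates use 182 per group, α = 0.025 and the planning SDs.

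| δ | Slope | Bias | Share of 0.267 | Power if attenuating | Power if inflating | Rejection with no true effect |
|---|---|---|---|---|---|---|
| 0.05 | 0.3 | 0.015 | 6% | 75% | 85% | 0.027 |
| 0.10 | 0.5 | 0.050 | 19% | 61% | 92% | 0.051 |
| 0.20 | 1.0 | 0.200 | 75% | 7% | >99% | 0.53 |

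The direction is open. If VR children are already calmer at T0, adjustment attenuates the effect. If they are more excited at T0, it inflates it.

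**4. VARS.** The pilot T0 mean was 0.08 (SD 0.28) on a 0 to 5 scale. A baseline this close to the floor leaves little room for a downward shift, so the main exposure is SAA.

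**The case against.** The strongest reply is that the order of sentences is not the order of events. Nothing in the text explicitly makes baseline follow the announcement; the baseline sentence only places it ahead of the dental procedure. The section is not strictly chronological either, since VARS, which has a T0 rating, is mentioned only after the sentence on how long the intervention lasts. The questionnaire is one of the baseline items, yet under Sociodemographic and Clinical Characteristics it is completed in the waiting room after consent. The misfit of 15 minutes into 10 itself suggests that some baseline work starts before login. A journal article may also leave the detailed sequence to the full protocol.

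Much of this stands. It rules out saying that the plan requires a post-allocation baseline. It does not remove the point: the article does state a sequence and durations, these conflict, and its T0 definition is met by a sample taken after the announcement.

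A reader might also infer more about the raters, namely that the person who opened the allocation makes all T0 ratings. The article says only that a research assistant scores VARS and VBRS, and it names no FLACC-R rater for this trial. The baseline sentence lists SAA but not VARS, so a late T0 VARS is an inference from Table 3 and the T0 definition.

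**Conclusion.** The point holds as a weakness in what the plan permits. T0 SAA, and by inference T0 VARS, may be measured after the arm is known, and both primary ANCOVAs adjust for T0. Over the assumed ranges the bias in log SAA is 0.015 to 0.20 against a planned 0.267. The size rests wholly on those assumptions, and the sign is unknown.

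Two stronger readings are not supported. First, one might treat both primary outcomes as change from T0 and conclude that a shift of 0.10 costs 0.10/0.267 = 37% of the planned effect. VARS is analysed as the T1 score with T0 as a covariate. For SAA, once T0 is a covariate, the full shift carries through only if the slope is 1, the upper limit of the range above. Second, one might conclude that randomization or allocation concealment is compromised. Neither is affected: the arm is released only after consent and the eligibility check.

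**What to change.** - Reconcile the timings in Study Proceedings, and state where familiarization sits relative to the start of the intervention.
- Define T0 as before the arm is disclosed.
- For remaining participants, require T0 SAA, T0 VARS and the other T0 measures to be completed before REDCap releases the arm, enforced by one completion field. With 300 of 400 recruited as of November 2025, this reaches at most about a quarter of the sample.
- For children already enrolled, compare T0 times with REDCap randomization times where T0 times were recorded. The article does not say that they were.
- If T0 followed disclosure, prespecify, before results are seen, a sensitivity analysis in all randomized children that compares T2 SAA (the level, not the change) and T1 VARS without T0 adjustment. Children measured late should not be excluded: that would conflict with the intent-to-treat approach and, if the narrated order was followed, could leave nobody to analyse.

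The cost is a re-ordering of existing steps, one REDCap field and one extra model per primary outcome. The models without T0 may be less precise. No extra visit or staff is needed. If T0 always preceded disclosure, one clarifying sentence, with the timings corrected, closes the matter.

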### Statistical Analysis

The primary analyses for this study will follow an intent-to-treat approach, using randomization status as the independent variable, and the mean difference in anxiety (using the anxiety subscale of the Venham) during the dental procedure (T1) and the SAA mean difference between T0 and T2 as the primary outcomes. As there are two primary outcomes (anxiety subscale and SAA), a Bonferroni correction will be applied, and a significance level of *P*=.025 will be used to determine statistical significance of primary outcomes. An ANCOVA, adjusting for unequal variances and adjusted for the time of the procedure, age, and baseline (T0) anxiety or behavioral score, will be used to assess the mean difference in Venham anxiety score during the dental procedure (T1) between the experimental and the control groups. An ANCOVA, adjusted for time of procedure, neurodevelopmental diagnosis, age, and baseline SAA level (T0), will be used to assess the mean difference in SAA level between groups 10 minutes after the procedure (T2).

For the secondary outcomes analyses, parametric tests adjusted for procedural type, age, sex, and parental presence will be used. Comparisons of dichotomous variables, including the necessity of procedural retakes, the use of other nonpharmacological interventions, and the occurrence of side effects, will be assessed using the Cochran-Mantel-Haenszel test. We will also perform subgroup analyses by age group (6‐12 y vs 13‐17 y) and sex and gender (boys, girls, or other) using ANCOVA. Any side effects will be reported using the Medical Dictionary for Regulatory Activities terminology [42], and their proportions will be compared between groups.

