**Methods:**

This randomized controlled trial follows a parallel design with two groups: a control group receiving standard care and an experimental group using VR. A sample size of 400 participants was calculated. Participants will be randomly assigned equally to each group. Recruitment will take place at the dental clinic of the Centre Hospitalier Universitaire Sainte-Justine, a tertiary- and quaternary-care center that primarily serves pediatric patients with SHCN. The two primary outcomes will include both observed and objective biomarker-based measures of anxiety. DFA will be evaluated using the Venham Anxiety Rating Scale as well as changes in mean levels of salivary alpha-amylase. Sociodemographic characteristics, parents’ and health care professionals’ satisfaction levels, participants’ pain intensity and behavior during the procedure, changes in heart rate, occurrence of side effects, procedure duration, and any deviations from normal procedural length will also be collected. Descriptive and comparative statistics will be conducted for demographic and clinical comparisons and will be used to present sociodemographic and clinical data, parents’ and health care professionals’ satisfaction levels, child satisfaction with the game, and procedural time.

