Factors in the dental setting that trigger DFA include loud dental instrument sounds, the presence of unfamiliar people examining the oral cavity, and fear of pain [17]. Of these, the biggest trigger of DFA is the anticipation and use of local anesthesia injections [9,17]. Although necessary for effective pain control during certain procedures, local anesthesia injections are understandably uncomfortable [9]. For children, the initial injection combined with the feeling of numbness during the procedure can be especially distressing [9]. Pharmacological agents, combined with light to moderate sedation or general anesthesia, can also be considered for noncooperative patients, who are often time-consuming and more costly and carry higher health risks [3]. In current research, audiovisual distractions such as tablets and TV screens have been used as additional distraction techniques beyond traditional tell-show-do methods, yielding overall positive results [18]. However, these techniques lack interactivity, resulting in less immersive distraction environments for children [19]. The lack of cooperation due to DFA often forces dentists treating pediatric patients to end appointments prematurely, sometimes without completing the planned procedures. Treating anxious and fearful patients can create a stressful environment for the clinician and the dental team [3]. Particularly when treating children with SHCN, extra time and tools are needed to ensure comfortable dental care. Depending on the child’s diagnosis, some may experience hypersensitivity to external stimuli such as loud noises, aversion to specific tastes, or difficulty straying from usual daily routines [20]. Furthermore, Pagano et al [20] showed that augmented reality was well suited for patients with autism spectrum disorder as preparation for their dental visits.

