### Interventions

#### Control Intervention

Participants assigned to the control intervention will only receive the care-as-usual approach. This includes viewing cartoons on a muted, mounted television already set by the clinic, watching a video of their choice on a tablet on YouTube, and the use of pharmaceutical treatment during the procedure, such as injected local anesthesia, if indicated by the procedure. In the event of noncooperation during the appointment, any necessary procedural retakes or rescheduling of appointments as determined by the dentist will be documented by the research assistant. One parent will be permitted to be present in the room during the procedure as part of the clinic’s usual protocol, and their presence will be recorded. Children in the control intervention will be offered the option to try the VR game after the study period, if they choose to do so.

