#### Measures of Secondary Outcomes

The secondary outcomes will be measured as follows:

Parents’ or legal guardians’ satisfaction with the intervention will be assessed using a Numerical Rating Scale (0‐10, where 0 is very dissatisfied and 10 is very satisfied) and according to the recommended question by the Pediatric Initiatives on Methods, Measurement and Pain Assessment in Clinical Trials: “Considering anxiety relief, side effects, and emotional recovery, how satisfied were you with the intervention used to manage anxiety experienced by your child?” [39] (Multimedia Appendix 1).Health care professionals’ satisfaction with the intervention will be assessed using a 6-question satisfaction questionnaire, with a range of scores from 1 to 4 (1=“Totally disagree,” 2=“Disagree,” 3=“Agree,” and 4=“Totally agree”; Multimedia Appendix 2).Child satisfaction with VR will be assessed using a 0‐10 numerical rating scale (where 0 is very dissatisfied and 10 is very satisfied; Multimedia Appendix 1).Physiological parameters (heart rate and oxygen saturation) will be measured using the COVIDIEN Nellcor pulse oxygen saturation meter, an approved and validated device.The patient’s behavior during the procedure will be assessed by proxy via a research assistant using the Venham Behavioral Rating Scale at T0 and T1 (Table 3) [25,40]. This 6-point scale assesses children’s behavior and provides information about patients with disruptive behavior. The scale points are based on objective, and readily observable behaviors and classify children’s behavior into 6 categories ranging from 0 (total cooperation) to 5 (general protest, no compliance, or cooperation). This scale has demonstrated good interrater reliability and has proven to be a valuable instrument for assessing children’s behavioral responses to dental procedures [40].Side effects will be collected in children in both groups from arrival on site until discharge, using a checklist of side effects commonly associated with VR, namely nausea, dizziness, and vomiting. Any of these side effects will be recorded along with the time they will occur.The length of the procedure in minutes will be measured and recorded for each participant and compared between the two groups.Pain will be assessed using the Face, Legs, Activity, Cry, and Consolability—Revised scale (FLACC-R) [41] (Multimedia Appendix 3). This questionnaire will serve to assess VR efficacy in reducing pain by comparing the mean pain level of both groups (experimental and control intervention) during the dental procedure (T1).

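### Both primary ANCOVAs leave out procedure type, the VARS model also leaves out neurodevelopmental diagnosis, and two of the covariates they do name are not pinned down

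*Protocol article*

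**What the plan says.** The Statistical Analysis section of the protocol article sets out three covariate lists.

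- **VARS at T1 (primary):** "adjusted for the time of the procedure, age, and baseline (T0) anxiety or behavioral score".
- **SAA at T2 (primary):** "An ANCOVA, adjusted for time of procedure, neurodevelopmental diagnosis, age, and baseline SAA level (T0").
- **Secondary outcomes:** "parametric tests adjusted for procedural type, age, sex, and parental presence will be used".

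Other sections bear on these lists:

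- Sample and Setting gives the range of procedures: examinations, prophylaxis, extractions and restorations. Sociodemographic and Clinical Characteristics has the procedure needed and the clinical diagnosis collected in the waiting room before the intervention.
- The Background states that "the biggest trigger of DFA is the anticipation and use of local anesthesia injections".
- Randomization and Allocation describes permuted blocks of random size and mentions no stratification factor.
- Procedure length is a secondary outcome: "The length of the procedure in minutes will be measured and recorded for each participant and compared between the two groups". The abstract lists "child satisfaction with the game, and procedural time" among the items to be presented.
- On parents, the Control Intervention section says "One parent will be permitted to be present in the room during the procedure", with presence recorded; the experimental arm has the same rule. The research assistant is to "log into REDCap only 10 minutes before the start of the intervention", obtain the allocation and announce it. There is no blinding of staff, participants or parents.

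**The concern.** A child having a cleaning and a child having an extraction under local anaesthesia face very different stress, and the Background says as much about injections. Procedure type is therefore a natural baseline covariate for an anxiety outcome. The plan uses it for the secondary outcomes but not for the two outcomes on which the trial will be judged. Neurodevelopmental diagnosis is treated as relevant to a salivary enzyme but not to VARS, which is scored on conversation, crying, body movement and response to verbal communication. What is at stake is precision, and protection against a chance imbalance in procedure mix or diagnosis between the arms.

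The second issue is the wording of the covariates that are listed. The time-of-procedure term could mean clock time or duration, and the two have very different consequences. The choice between an anxiety and a behavioural baseline score in the VARS model is left open. Both leave room for a decision after the data are seen in a primary analysis.

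**Working it through.** **1. The plan's own figure.** Sample and Setting gives 364 participants (182 per group). Inputs from that section: log-SAA changes of 0.171 (SD 1.05) and −0.096 (SD 0.495), so a difference of 0.171 − (−0.096) = 0.267; power 80%; two-sided α = .025 after Bonferroni. A Welch two-sample t test with these inputs needs 182 per group (power 0.801), which reproduces 364. No covariate enters the calculation, so planned power does not depend on the covariate lists. Any gain from adjustment comes on top.

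**2. Covariate lists side by side.**

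| Covariate | VARS (primary) | SAA (primary) | Secondary |
|---|---|---|---|
| Procedure type | no | no | yes |
| Neurodevelopmental diagnosis | no | yes | no |
| Age | yes | yes | yes |
| Sex | no | no | yes |
| Time of procedure | yes, undefined | yes, undefined | no |
| Baseline score | anxiety or behavioural | SAA | not stated |
| Parental presence | no | no | yes |

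**3. Precision given up.** Let R² be the share of residual variance that the added baseline covariates explain. The documents give no value; 10–20% is an assumption. Confidence-interval width scales by √(1 − R²), and the equivalent gain in sample size is 1/(1 − R²).

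- R² = 0.10: √0.90 = 0.949, intervals about 5% narrower; 1/0.90 = 1.11. Equivalently, 400 × 0.90 = 360 adjusted participants match 400 unadjusted.
- R² = 0.20: √0.80 = 0.894, about 11% narrower; 1/0.80 = 1.25. Equivalently, 400 × 0.80 = 320.

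**4. If time of procedure meant duration.** Two illustrations follow, both on assumed values.

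- *Duration driven by the outcome.* With Y = βT + e and D = γY + u, the coefficient of T given D is β(1 − ρ²), where ρ is the within-arm correlation of Y and D. At ρ = 0.3 the factor is 0.91 (9% shrinkage); at ρ = 0.5 it is 0.75 (25% shrinkage).
- *VR changes duration directly, with no true effect on the outcome.* Suppose a latent distress trait has correlation 0.5 with both duration and outcome. The within-arm covariance is then 0.5 × 0.5 = 0.25, and the adjusted estimate is off by −0.25 times the shift in duration. For shifts of 0.25, 0.5 and 1.0 SD this is about −0.06, −0.12 and −0.25 SD. In simulation (400 participants, 1,000 repeats, α = .025) the null was rejected in about 6%, 15% and 53% of trials, against about 3% unadjusted.

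With no effect of VR on duration in the second set-up, there was no bias. Scheduled clock time is fixed by the appointment, so adjusting for it raises no such problem.

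**5. Parental presence.** It enters only the secondary models. The arm is announced before an open-label procedure, so presence could respond to it, but no section says when presence is settled. The holding of restless children, under Study Proceedings, concerns parental involvement, which is recorded as a separate item.

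**The case against.** The strongest reply is that omitting a prognostic covariate is a matter of efficiency: the randomised comparison stays valid, and the sample size was set without covariates. That is right, and the point is confined to precision and chance imbalance. It is still worth making, because the variables are already collected and the plan itself adjusts for procedure type elsewhere.

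A second reply is that an observer rating and a biochemical marker may properly have different covariates, with reasons given in a fuller document, and that a condensed article may omit a stratification factor. Both are possible. Neither explains leaving procedure type out of both primary models.

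Third, changing primary covariates late has a credibility cost: the trial is unblinded and 300 participants had been recruited by November 2025. This stands, and is why the change must be documented and made before the analysis.

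Several stronger readings are tempting but not supported:

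- *The primary models adjust for parental presence.* They do not, and nothing shows that allocation affects presence.
- *The plan adjusts for duration.* The body of the article otherwise says length or duration; only the abstract's procedural time points the other way. Clock time is a plausible reading, so the fault is an undefined term.
- *Procedure type is the strongest predictor available.* The Background ranks injections as a trigger but names past traumatic dental experience as the most predictive factor, and gives no association of procedure type with VARS or SAA.
- *Baseline VARS is useless as a covariate.* The pilot (25 children, mean 0.08, SD 0.28) suggests a floor, but no T0–T1 correlation is reported.

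**Conclusion.** The point holds as one of precision and specification. Both primary ANCOVAs omit procedure type, and the VARS model omits neurodevelopmental diagnosis, although both can be had from information recorded before the intervention. The cost is confidence intervals wider than they need be. The 5–11% figure rests wholly on the assumed R² of 10–20%. There is no bias from these omissions.

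Separately, the time-of-procedure term and the baseline score in the VARS model are not uniquely defined. The first is harmless if it means scheduled clock time. It could distort a primary result if implemented as duration, by an amount that depends on assumptions the documents cannot settle. Parental presence is a lesser matter for the secondary analyses only: it could be affected by allocation, and is not shown to be.

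**What to change.** - In both primary ANCOVAs, adjust for planned procedure type as recorded before the intervention, neurodevelopmental diagnosis, age, and the T0 value of the same outcome (VARS for VARS, SAA for SAA). This removes the choice between anxiety and behavioural score.
- State that time of the procedure means scheduled clock time, and that procedure duration is not a covariate in either primary model.
- In the secondary models, drop parental presence as a covariate or report it by arm, noting that it could be affected by the open-label allocation.

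The cost is a few degrees of freedom in a trial of 400 and a dated, documented change to the analysis plan. No new data are needed. To keep its credibility, the change should be recorded before any outcome comparison by arm is run, with results expected in June 2026.
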